#### App functionality during the technical training

During the technical training, the EMA module and Graphical Overview Feedback module of the app will be active. The EMA module of the Think Slim app will be used to obtain real-time data of eating-related variables. Items that are part of the EMA questionnaires include measures of food desire strength, specific food desires, emotions, cognitions, locations, activities, social company and food consumption. During the training, EMA will be performed at two separate instances: (1) eating events (event sampling), and (2) eight times pseudorandomly throughout the day (time-contingent sampling). Sampling of an eating event will be initiated by the participants themselves, whereas time-contingent sampling points will be generated by the app. Note that cognitions and food consumption will only be assessed during eating event sampling. Otherwise the eating event samples and time-contingent samples are the same. The first time-contingent sample of the day will also assess sleep duration and quality. Beverage consumption will be assessed in a separate assessment, which will occur prior to bedtime.

In addition to the EMA module, graphical overview feedback will be accessible in a separate section of the app. The feedback will represent pie charts of the activities and locations assessed at eating event samples by the participant, separately for foods that are considered healthy and unhealthy. In addition, a line graph of desire strength and strength of various emotions, presented relative to time, will be available. The graphical overviews will continuously be updated, as soon as new EMA data is entered into the app. To generate the overviews, at least one eating event sample is necessary.

#### Randomisation

After completing the technical training, all participants will be contacted by the researchers to discuss possible issues that occurred during the training. Subsequently, randomisation will take place. Participants will be randomly assigned to either the immediate intervention group or the diet-only control group using computer-generated randomisation via Research Randomizer (www.randomizer.org). More specifically, randomisation is pre-stratified by age group (18–30; 31–40; 41–50; 51–60) and gender. For each age group, separately for male and female participants, each participant will be assigned a randomly generated number. Half of the participants with the largest randomly generated numbers will be assigned to the immediate intervention group, whereas the other half will be assigned to the diet-only control group. Note that participants who indicate as being unavailable during a specific time period, due to for example holidays, will be manually allocated to the condition that matches with their availability. Blinding participants and researchers is not possible in the current setup.

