## Methods

### Trial design

A randomised controlled superiority trial will be conducted, in which 134 overweight (BMI above 25 kg/m^2^) participants will follow a diet of their own choice. In addition, they will exercise according to their own personal exercise plan. Participants are split into two groups. The two groups will run in parallel. The immediate intervention group (*n* = 67) will immediately receive the Think Slim intervention in addition to their chosen diet. During this time, the diet-only control condition group (*n* = 67) will receive no further support. The diet-only control condition group will receive the Think Slim intervention after the immediate intervention group has completed the intervention. The enrolment procedure is graphically shown in Fig. 1. The trial has been approved by the Ethics Committee of the Faculty of Psychology and Neuroscience of Maastricht University (The Netherlands), and is registered at the Dutch Trial Register, part of the Dutch Cochrane Centre (NTR5473). The study will adhere to recommendations of the Consolidated Standards of Reporting Trials (CONSORT) [54].

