#### Phase 3: Intervention Phase (weeks 2–7)

After the first EMA-only week, the Intervention Phase starts. This phase has a total duration of 6 weeks (weeks 2–7).

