#### Diet

During the Intervention Phase, all participants (immediate intervention group and diet-only control group) are asked to actively follow a calorie-restrictive diet of their own choice. Supervision of the diet by a dietician or healthcare professional is not allowed. Instead, all participants select a diet coach (friend or family member). Participants will also develop an exercise plan. General information about dieting and exercising is provided as part of two online sessions in the first week of the Intervention Phase. At the end of the first week, participants are asked to finalise their choice. Aside of the two online sessions, no further information about selecting a diet is provided.

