#### App functionality during the Intervention Phase

Participants in the diet-only control group will not be able to use the app during the Intervention Phase. For these participants, all app functionality will be blocked. Instead, the app will display the number of days remaining until the end of the waiting period. Eight days before the end of the waiting period, the app will send a notification informing participants that the end of the waiting period is near.

For participants in the immediate intervention group, app functionality in the first week of the Intervention Phase will consist of the EMA module and the Graphical Overview Feedback module, similar to the training and the first EMA-only week. In addition, the Adaptive Feedback module will be active. The Adaptive Feedback module provides participants with feedback if they are at risk for overeating. The feedback message consists of a generic warning and a behavioural advice. Detection of a participant’s ‘risky’ moments is based on the answers provided by the participant on the EMA items. To estimate when the participant is likely to eat something unhealthy in the time-period directly following a completed time-contingent sample, the sample data is compared to a set of allocated pre-existing rules that indicate what combinations of states of variables (e.g. scoring high on desire + being at home + feeling bored + feeling calm) are predictive of unhealthy eating. If there is a match between the time-contingent sample and one of the rules, the participant receives adaptive feedback messages via the Think Slim app.

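### Participants who report being unavailable are placed in an arm by hand rather than randomised, and the article sets no limit on this and no separate handling in the between-group comparison

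*Protocol article*

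**What the plan says.** Under Trial design the article announces: "A randomised controlled superiority trial will be conducted". Under Randomisation it gives the method: "Participants will be randomly assigned to either the immediate intervention group or the diet-only control group using computer-generated randomisation via Research Randomizer". The draw is stratified by age group and gender, and within each stratum the participants with the larger random numbers go to the immediate arm.

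The same paragraph then makes an exception. Participants who report that they are unavailable in a given period, "due to for example holidays, will be manually allocated to the condition that matches with their availability". The next sentence adds: "Blinding participants and researchers is not possible in the current setup".

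The timetable comes from the later sections:

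- **Diet:** in weeks 2–7, "all participants (immediate intervention group and diet-only control group) are asked to actively follow a calorie-restrictive diet of their own choice".
- **Cognitive intervention:** in those weeks the immediate arm also has ten online sessions. Five are due in the first intervention week, and dropout rules apply to sessions not completed on time.
- **App functionality during the Intervention Phase:** "Participants in the diet-only control group will not be able to use the app during the Intervention Phase".
- **Phase 5:** the control arm receives Think Slim in weeks 9–14, followed by an EMA week in week 15.
- **App functionality during the Intervention Phase, last paragraph:** the second weight measurement is taken in week 8.

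Data analysis sets out group-by-time ANOVAs under intention-to-treat and completers principles. It does not mention the hand-placed participants.

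**The concern.** A participant whose arm follows from declared availability has not been randomised, whatever the trial is called. If availability is related to the outcome, the arms differ systematically before treatment starts. Being away from home during a self-chosen diet is a plausible influence on six-week weight change.

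The planned safeguards do not reach this. Stratification covers only age group and gender. The inspection of baseline differences cannot show who will be away later. Intention-to-treat keeps the assignment as it was made, and here that assignment is the problem. Staff who know the arms make the placement, so for these people allocation is also known in advance.

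At stake is the primary comparison of BMI change, and every secondary comparison between the arms over the same weeks. The long-term analysis, which collapses over group, does not rest on the allocation.

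**Working it through.** **Step 1: which arm matches whom.** The article does not say, so this is reasoned from the timetable.

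| Weeks | Immediate arm | Diet-only arm |
|---|---|---|
| 1 | EMA week, baseline | EMA week, baseline |
| 2–7 | Diet, ten cCBT sessions, app, session-based dropout rules | Diet, two online information sessions in the first of these weeks, app blocked |
| 8 | EMA week, weight | EMA week, weight |
| 9–15 | Follow-up has begun | Think Slim (weeks 9–14), EMA week (week 15) |

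Someone away in weeks 2–7 fits the control arm better, because the session load and dropout rules fall on the other arm. That person is still expected to diet, and is weighed in week 8. Someone away in weeks 9–15 fits the immediate arm, and may well be at home in weeks 2–7. If absence hinders dieting, both flows worsen the control result relative to the immediate result.

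**Step 2: size.** The article gives neither the number hand-placed nor the effect of being away. Both are assumptions here:

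- f = share of the whole sample away in weeks 2–7: 5%, 10% or 20%
- g = how much worse their BMI change is: 0.2 to 0.5 SD
- all of them are placed in control, and the randomised participants fill the arms to equal size (67 each, as in Trial design)

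The control arm is half the sample, so its share of away participants is f / 0.5, and the immediate arm has none:

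bias = g × f / 0.5

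The rejection rate when there is no true effect uses the noncentral t distribution with 51 per arm (the completing number in Sample size), 100 degrees of freedom and noncentrality bias × √(51/2), two-sided at 5%.

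| f | People (of 134) | Share of control | Bias, g = 0.2 | Bias, g = 0.5 | Two-sided type I error |
|---|---|---|---|---|---|
| 5% | 6.7 | 10% | 0.02 SD | 0.05 SD | 5.1–5.7% |
| 10% | 13.4 | 20% | 0.04 SD | 0.10 SD | 5.5–7.9% |
| 20% | 26.8 | 40% | 0.08 SD | 0.20 SD | 6.9–17.0% |

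Against the design effect d = 0.5, this runs from 0.02/0.5 = 4% to 0.20/0.5 = 40%.

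**Step 3: how far the assumptions matter.**

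- *Arms not held equal.* If the randomised participants are split evenly and the hand-placed are added to control, the 10% case gives 13.4 / (13.4 + 60.3) = 18% of control and a bias of 0.036–0.091 SD. The 20% case gives 26.8 / (26.8 + 53.6) = 33% and 0.067–0.167 SD.
- *Hand-placed people in both arms.* If 10% of the sample is hand-placed, half for absence in weeks 2–7 and half for absence in weeks 9–15, only the first half is away while dieting, and the 5% row applies.
- *People away in weeks 2–7 not all sent to control.* With three quarters in control and one quarter in the immediate arm, the bias halves: g × (0.75f − 0.25f) / 0.5. With an even split it is zero.

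**The case against.** **The direction is not written down.** A reader might infer that the protocol steers people on holiday into the control arm. The article says only that the arm must match availability. It does not say which weeks count or how long an absence has to be, and holidays are only an example. The sessions are online, take about 25 minutes each, and one may be late after the first intervention week, so a short absence need not rule out the immediate arm. Control participants also have duties in weeks 1, 2 and 8. This stands: the direction is a likely reading of the timetable, not a stated fact.

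**Silence is not a decision to pool.** A reader might infer that the plan analyses these people as if randomised. Data analysis neither includes nor excludes them, and a fuller protocol or an SAP could deal with them. This stands as to wording. It does not rescue the rule, since no analysis plan can make the assignment random afterwards.

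**The size could be made to look large.** With an effect of 0.8 SD and 20% of the sample all placed in a control arm of 67, the bias would be 0.8 × 0.40 = 0.32 SD, or 64% of d = 0.5. The documents support neither the effect nor the one-way placement.

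**The design label and the lack of blinding are not errors in themselves.** Blinding is not feasible in this comparison. The point here is the allocation rule.

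**Conclusion.** The point holds. The article states a rule under which some participants are not randomised, places no limit on their number, and names no separate handling in the between-group analysis. That much needs no assumption.

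That the rule favours Think Slim is likely, on the grounds that only the immediate arm carries sessions, app use and dropout rules in weeks 2–7 while both arms diet. It also depends on absence worsening weight change.

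The size cannot be determined. Under the stated assumptions it is about 0.02–0.20 SD of BMI change. It is small if few people are affected, and smaller than the table shows if part of a given hand-placed group goes to the immediate arm. At the upper end it would matter against a design effect of 0.5 SD. Because the rule has no cap, the article does not exclude that end.

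**What to change.** 1. Delete the manual-allocation rule.
2. Ask about availability at the contact that already takes place after the technical training and before randomisation. Anyone who could not follow whichever of the two schedules the draw might give starts later, and is randomised once either arm is possible.
3. For anyone already hand-allocated, report the number per arm and leave them out of the primary randomised comparison and the other between-group comparisons. Show a sensitivity analysis that includes them. Their status was fixed before any post-intervention outcome, so leaving them out does not depend on results. They can stay in the long-term analysis that collapses over group.

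**Cost.** A short amendment while the trial is still recruiting, a later start for some participants, and a loss of sample size equal to the number already hand-allocated. That number should be stated. At 5%, 10% or 20% of 134 it would be about 7, 13 or 27 people, and the last is not trivial. On a separate matter, the stated 80.6% power with 51 per arm and d = 0.5 reproduces only as a one-sided figure. The two-sided t-test gives 70.6%, so there is little room for loss, and replacing the excluded participants should be considered.

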#### Phase 2: EMA-only week 1 (week 1)

The trial starts with an EMA-only week. At the start of this week, all participants (immediate intervention group and diet-only control group) will fill out a baseline assessment consisting of several self-report questionnaires (specified below, under ‘Measures’) about eating styles, eating disorder pathology, general psychological distress, self-esteem and dysfunctional thinking. In addition, participants will obtain an independent measure of their BMI. No further intervention will take place.

#### App functionality during the first EMA-only week

During the entire week, the EMA module and Graphical Overview Feedback module of the app will be active, identical to the technical training.

#### Phase 3: Intervention Phase (weeks 2–7)

After the first EMA-only week, the Intervention Phase starts. This phase has a total duration of 6 weeks (weeks 2–7).

#### Diet

During the Intervention Phase, all participants (immediate intervention group and diet-only control group) are asked to actively follow a calorie-restrictive diet of their own choice. Supervision of the diet by a dietician or healthcare professional is not allowed. Instead, all participants select a diet coach (friend or family member). Participants will also develop an exercise plan. General information about dieting and exercising is provided as part of two online sessions in the first week of the Intervention Phase. At the end of the first week, participants are asked to finalise their choice. Aside of the two online sessions, no further information about selecting a diet is provided.

#### Cognitive intervention (for immediate intervention group only)

The cognitive intervention will be aimed at changing obesity-related dysfunctional thinking and at increasing self-esteem. It consists of ten individual online sessions on a computer (cCBT), and a module in the app. The computer sessions are included because CBT requires explanation of the theoretical model and therapeutic concepts that are too comprehensive to provide via an iPhone app due to screen size limitations that prevent a convincing digital presentation of the intervention. Therefore, the online sessions provide participants with the necessary information on the cognitive model and cognitive techniques, whereas the app is suitable to practise these skills in daily life.

There are a total of ten online sessions of approximately 25 minutes that will be delivered via an in-house web-environment for online therapy and questionnaire research (SOTO). To start each session, participants receive an e-mail with a link to the SOTO web-environment. The sessions are based on several CBT for weight loss protocols [45, 58, 59]. They are designed to be provided in addition to a standard calorie-restrictive diet. Table 1 contains a brief summary of each session’s contents. In the first week of the Intervention Phase, five sessions will take place. In these sessions, participants will determine reasons for losing weight, set dietary goals, choose a diet, make an exercise plan, and make a list of techniques to distract from food craving. All information except the choice of diet and exercise plan will be accessible for review in the app. Furthermore, participants will be familiarised with the cognitive model and basic cognitive techniques. They will also learn how to identify and evaluate dysfunctional cognitions, and how to replace these with alternative cognitions that are more helpful towards eating behaviour and dieting. For the first week, all five sessions will need to be completed at the end of the week. Participants who do not complete all five sessions will be considered dropouts. Participants will be sent reminder e-mails in case they lag behind and will be contacted by the research staff in case they are close to being considered dropouts.

**Table 1 Tab1:** Summary of the contents of the computerised cognitive behavioural therapy (cCBT) sessions

#	Theme	Description
1.	Introduction	Information on weight-gain and weight-loss Introduction of the cognitive model and the concept of dysfunctional thinking Information on how to select a diet, diet coach and exercise plan^a^
2.	Motivation	Personal reasons for losing weight^b^ Realistic weight loss goals^b^ Identifying and responding to sabotaging cognitions about dieting Personal list of sabotaging cognitions about dieting^b^
3.	Coping with food desire	Information on the difference between hunger and food desire Tips on how to deal with food desire Personal list of distraction techniques^b^
4.	Identifying dysfunctional cognitions	Identifying dysfunctional cognitions about eating Introducing the concept of dietary temptations Instruction on how to do this in the app
5.	Responding to dysfunctional cognitions	Introduction of socratic questioning Information on how to construct functional alternative cognitions Instruction on how to do this in the app Choosing a diet and exercise plan^a,c^
6.	Thinking errors	Summary of basic CBT skills Introduction of concept of thinking errors Instruction on how to do this in the app
7.	Interim evaluation	Evaluation on progress so far^c^ Increasing motivation Learning to compliment oneself
8.	Self-esteem: body	Positive body exposure
9.	Self-esteem: person	Designing a positive portrait of the self^c^
10.	Evaluation and relapse prevention	Summary of intervention^c^ Evaluation of intervention Creating a relapse prevention plan^c^

Note: the content of these sessions is derived from several cognitive behavioural therapy (CBT) protocols [45, 58, 59].

^a^component is completed by immediate intervention and diet-only control groups simultaneously; ^b^information is transferred to the app for review; ^c^information will be sent to participants by e-mail; in each session, the level of dysfunctional thinking will be assessed by believability ratings (visual analogue scales (VASs)) of nine frequently occurring dysfunctional cognitions about eating

From the second week until the last (week 7) of the Intervention Phase, participants will complete additional cCBT sessions at the end of each week (sessions 6–10). In these sessions, cognitive skills are reviewed, and participants are encouraged to stay motivated. Furthermore, self-esteem is addressed in two sessions, focusing on the body and on personality characteristics. In the final session special attention is paid to evaluation and relapse prevention. All online cCBT sessions will be completed without therapist involvement. Participants are allowed to lag behind one session, and will be considered dropouts if more than one session is not completed on time. At the beginning of each session, dysfunctional thinking will be assessed via a self-report questionnaire. Participants in the diet-only control group will not receive any cognitive intervention during the Intervention Phase.

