### Data analysis

Participant’s flow from screening to randomisation will be mapped out. Furthermore, pre-treatment characteristics of the sample will be explored, and baseline differences between conditions will be examined in terms of size and clinical importance. Distributions of outcome variables will be inspected via histograms and boxplots. After that, intervention- and study-compliance will be determined, followed by an evaluation of participants’ satisfaction with the Think Slim intervention.

To test the effectiveness of the Think Slim intervention, 2 (group: immediate intervention versus diet-only control group) × 2 (time: pre versus post) analyses of variance (ANOVAs) will be run for the set of dependent variables (i.e. BMI, dysfunctional thinking, scores for questionnaires on eating styles, eating disorder pathology, general psychological symptomatology, and self-esteem). Long-term effects of the Think Slim intervention on the set of dependent variables will be examined using one-way repeated-measures ANOVAs collapsing over group (i.e. for all 102 participants), with four levels: pre-Think Slim, post-Think Slim, 3-month follow-up and 12-month follow-up. All analyses will be performed according to the intention-to-treat principle [69] and the completers principle. Lastly, time-lagged multilevel network analyses will be conducted on data obtained during the pre- and post-Intervention Phase EMA-only weeks, to assess changes in patterns of data that result in unhealthy eating [31, 37]. Changes in network connectivity between the pre- and post-Intervention Phase networks will be compared between both conditions. Of particular interest are changes in network connectivity and density related to unhealthy eating, in terms of graph analysis measures such as indegree, outdegree, betweenness, and centrality of network nodes.

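### Missed online sessions make a participant a dropout in the intervention arm only, so the completers version of the pre-post comparison is not a randomised contrast, and the plan does not say whether it or intention-to-treat decides

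*Protocol article*

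**What the plan says.** All places are in the Protocol article.

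- **Intervention arm.** Two session rules stand in the section on the cognitive intervention, whose heading limits it to the immediate intervention group. For the five sessions of the first intervention week: "Participants who do not complete all five sessions will be considered dropouts". For sessions 6–10: "Participants are allowed to lag behind one session, and will be considered dropouts if more than one session is not completed on time". The same section ties retention effort to session progress: "Participants will be sent reminder e-mails in case they lag behind and will be contacted by the research staff".
- **Control arm, weeks 2–7.** That section also states: "Participants in the diet-only control group will not receive any cognitive intervention during the Intervention Phase". Under App functionality during the Intervention Phase, the controls' app is blocked. Their online content is described under Diet and applies to both arms: "General information about dieting and exercising is provided as part of two online sessions in the first week of the Intervention Phase". No dropout consequence is attached to it.
- **Control arm after week 8.** Under Phase 5, controls follow the same Think Slim procedure in weeks 9–14, after the randomised pre-post comparison is over.
- **Analysis.** Under Data analysis the effect is tested with group-by-time ANOVAs (two groups, pre versus post), and: "All analyses will be performed according to the intention-to-treat principle [69] and the completers principle". No order of priority is given. The long-term analysis, which pools the groups, is described as covering 102 people.
- **Attrition.** Under Sample size, a single rate of 23.5%, taken from published EMI studies, raises 51 per arm to a total of 134.

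**The concern.** The article does more here than leave a definition open. It fixes a rule that turns treatment non-adherence into dropout, the rule can operate in only one arm during the randomised comparison, and the article then commits every analysis to a completers version.

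People who keep up with ten online sessions may well be the people who keep to a diet whatever they are offered. If the less adherent are removed from one arm only, the remaining means can differ even when the intervention does nothing. Because the plan does not say which analysis decides, a positive completers result beside a null ITT result would have no agreed interpretation.

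**Working it through.** **1. The plan's own attrition figure.** 51 / (1 − 0.235) = 66.7, so 67 per arm and 134 in total. This reproduces. In the other direction, 2 × 51 = 102, so the 102 in the long-term analysis is the number left after attrition, not the number randomised.

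**2. Who can be filtered, weeks 2–7.**

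| | Immediate intervention | Diet-only control |
|---|---|---|
| Sessions in the week | 5 in the first intervention week, then sessions 6–10 | 2 information sessions in the first intervention week |
| Session-based dropout rule | Yes | None stated |
| Reminders tied to session progress | Yes | None stated |

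**3. Size of the bias in the completers contrast.** Suppose the true effect is zero and BMI change has SD 1. Let r be the correlation between latent adherence and BMI loss. Removing the least adherent fraction q of an arm shifts the mean of those who remain by r × k(q), where k(q) = φ(z_q) / (1 − q).

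Inputs:
- 67 per arm and two-sided α = 0.05 are from the article.
- q = 23.5% in the intervention arm is borrowed from the article's overall attrition rate as an illustration. It is not a stated forecast for the session rule.
- r = 0.1–0.5 is an assumption. The article gives no figure.

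Constants: k(0.235) = 0.3073 / 0.765 = 0.402; k(0.10) = 0.1755 / 0.90 = 0.195; k(0.15) = 0.2332 / 0.85 = 0.274.

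The spurious difference is r × [k(0.235) − k(q_control)]. False-positive rates come from the noncentral t distribution, with about 51 people left in the intervention arm and 67 × (1 − q_control) in the control arm.

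| Control loss on the same trait | r = 0.1 | r = 0.2 | r = 0.3 | r = 0.5 |
|---|---|---|---|---|
| 0% | 0.04 SD; 5.5% | 0.08 SD; 7% | 0.12 SD; 10% | 0.20 SD; 19% |
| 10% | 0.02 SD; 5.1% | 0.04 SD; 5.5% | 0.06 SD; 6.2% | 0.10 SD; 8.4% |
| 15% | 0.01 SD; 5.1% | 0.03 SD; 5.2% | 0.04 SD; 5.4% | 0.06 SD; 6.2% |
| 23.5% | 0; 5% | 0; 5% | 0; 5% | 0; 5% |

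A simulation with 40,000 replicates per setting agrees with the first row (biases 0.039, 0.081, 0.121 and 0.202 SD; rejection 5.5%, 7.0%, 10.2% and 19.4%).

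**4. Equal numbers lost are not enough.** If controls also lose 23.5%, but for reasons unrelated to outcome, the simulated bias stays at 0.04–0.20 SD and the false-positive rate is 5.3–17.9%. Only loss selected on the same trait cancels it.

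**5. Other removal rates.** With no control loss on the trait, r = 0.1–0.5 gives 0.03–0.14 SD at q = 15% and 0.06–0.29 SD at q = 35%. Against the design effect d = 0.5, the 0.04–0.20 SD at q = 23.5% is 8–40%.

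**6. ITT.** If everyone randomised is measured and analysed as allocated, the expected bias from this source is zero.

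**The case against.** The strongest reply is that the article never defines a completer. The word could mean anyone with a post-intervention weight, a criterion that applies to both arms, and defining and ranking analysis sets is commonly left to a fuller document. Reporting completers beside ITT is also ordinary practice. This stands in part: the link between the session rules and the completers set is the natural reading, not a stated one. It does not remove the point, because the article itself uses the term dropout for missed sessions in one arm.

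Controls may also select themselves out. They spend six weeks with a blocked app, and those whose diet fails may not return for the week-8 weight. This stands too, and it is why the first row of the table is the upper end for a given r.

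Three stronger readings are tempting, and the documents do not support them:

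- *That the sample size plans for the session rule to reduce 67 to 51.* The 23.5% is an overall literature rate applied to both arms and is not linked to the rule.
- *That the ITT result is biased too.* Nothing says declared dropouts go unmeasured, and the instruction to obtain a week-8 weight does not exempt them. The figure of 102 suggests that dropouts leave the data, but only in the long-term analysis, where both groups have by then come under the same session procedure.
- *That the plan gives the two analyses equal weight, or that the bias certainly favours Think Slim.* The plan states no priority, which is not a statement of equality. The direction depends on adherence going with weight loss.

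**Conclusion.** The concern holds for the completers version of the pre-post comparison. On the natural reading, that analysis filters one arm on a behaviour for which the other arm is not filtered, and it stands beside ITT without a stated order. The size is uncertain because it depends on an undocumented correlation, on how many participants the session rule removes, and on whether controls are lost on the same trait. Under the illustrative settings it runs from zero to 0.20 SD, with a false-positive rate between 5% and 19%. The top of that range needs r = 0.5 and no control loss on the trait. ITT is exposed only if declared dropouts are not followed up, which the article does not settle. This should be corrected, but it does not invalidate the design.

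**What to change.** 1. For analysis purposes, label participants caught by the two session rules as non-adherent to sessions rather than as dropouts.
2. State that week-8 weight, questionnaires and both follow-up measurements are requested from every randomised participant, whatever sessions were done.
3. Name ITT on all 134 randomised as the deciding analysis of the pre-post contrast, and reconcile the 102 in the long-term analysis with the ITT commitment.
4. Keep the completers analysis as supportive only, with a criterion that can be met or failed in both arms, for example post-intervention BMI obtained. It remains a post-randomisation selection and should be reported as such.

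A complier-average estimate need not replace the completers analysis. Someone below the session threshold may still have had several sessions and the app modules, so the assumption that assignment has no effect on non-compliers is doubtful.

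The cost is a wording change plus some extra reminders and follow-up of non-adherent participants. The article gives the trial status as recruiting, so outcomes not yet due could still be secured.
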